### Randomization and blinding

Randomization will occur on the date of craniotomy aneurysm clipping. Permuted block will be used and stratified by the culprit vessel sites, including the middle cerebral artery, anterior cerebral artery, anterior communicating artery, and posterior communicating artery. The ophthalmic artery, internal carotid artery, and posterior circulation arteries will not be included in this study. The randomized digital table was previously computer (STATA 17) generated by dedicated independent staff and loaded into a web-based database. The allocation information will be obtained by the attending anesthesiologist through mobile phone software after the patient enters the operating room. Patients will be randomly allocated to receive either e-SGB or camouflaging in a 1 to 1 ratio. The endpoint assessors, data statisticians, and postoperative treatment team members will be blinded to the treatment group allocation, but the anesthesiologist and neurosurgeons will not be blinded, as they need to participate in the safe administration of related patient care. Patients will be unblinded only if they experience serious adverse events requiring additional visits.

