### Intervention

Randomized patients will receive an additional e-SGB or a “camouflage” operation before anesthesia induction and then receive standard care after the operation. In the intervention group, e-SGB will be performed by a designated experienced anesthesiologist using the B-ultrasound visualization technique. The intervention site will be the ipsilateral side of the planned craniotomy site. After routine disinfection, 8–10 mL of 0.5% ropivacaine will be injected into the surface of the longus colli muscle on the medial side of the prevertebral fascia at the level of the C6 anterior tubercle (Fig. 2), and the puncture point will be covered with sterile dressings. The success criterion of e-SGB is Horner's syndrome, which is characterized by miosis, ptosis, enophthalmos, conjunctival hyperemia, and facial redness without sweating. The patient will be monitored for at least 30 min before anesthesia induction to rule out any related complications after SGB. Patients with failed e-SGB will be excluded. In the control group, a blank control was adopted to reduce unnecessary invasive operations. Patients will not undergo any sham procedures and will only be prospectively visited at a specified time point. However, they need to undergo the “camouflage” operation to ensure the smooth implementation of the blinded endpoint evaluation. The anesthesiologist will cover the corresponding part of the patient with sterile dressings to confuse the follow-up, without any puncture. In this way, the follow-up staff would not be aware of the grouping of the participants by the puncture point. All patients will be admitted to the ICU after the operation and then receive the standard of care.

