### Statistical analysis

All efficacy and safety analyses will be analyzed on both a per-protocol and intention-to-treat basis. The intent-to-treat (ITT) population will comprise all subjects randomized to receive e-SGB and with the completed assessment of symptomatic CVS. The per-protocol (PP) population will consist of all subjects in the ITT population not identified as protocol violators (i.e., no obvious Horner’s syndrome after e-SGB, etc.). These protocol violations will be shown in a listing. Subjects with puncture interruption and abandonment due to various reasons are considered to have failed e-SGB and will be excluded from any form of analysis. The decision to exclude a subject from the PP population will be made prior to breaking the blind. The primary outcome will be compared between groups using the Cochran–Mantel–Haenszel test. Postoperative cerebral hemodynamic changes measured at multiple planned time points will be compared using repeated-measures analysis of variance (ANOVA) with the Tukey–Kramer test. In addition, repeated-measures ANOVA will be utilized with a mixed-model approach (including time as a random effect), and the specific comparison of the change in each of those measurements between baseline and any specific time point will be tested using linear contrast. For other outcome data, categorical data will be analyzed by the *χ*^2^ test, and continuous data will be analyzed using Student’s *t* test or the Mann–Whitney *U* test. The rates of spasm, death, complications, and length of stay in the hospital and intensive care unit will be compared using Cox proportional hazards models. All analyses will be adjusted by age, sex, preoperative Hunt-Hess score, preoperative Fisher grade, and site of aneurysm. For the missing data, the last observation and the worst-case imputation scenarios will be used as the main interpolation method. A *p* value less than or equal to 0.05 (two-tailed alpha level) will be considered statistically significant.

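### The only violation named for the per-protocol set can occur only in the e-SGB arm, so deciding exclusions before unblinding gives no allocation-blind protection for it, and freedom from outcome data is not stated

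*Protocol article*

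**What the plan says.** In the Statistical analysis section, all efficacy and safety analyses are run on both the PP and the intention-to-treat set, and neither is named as primary. PP subjects are those "not identified as protocol violators (i.e., no obvious Horner’s syndrome after e-SGB, etc". The section adds "These protocol violations will be shown in a listing" and, on timing, "The decision to exclude a subject from the PP population will be made prior to breaking the blind".

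A second rule in that section also concerns the puncture: if it was broken off or given up, the patient counts as a block failure and is dropped from every analysis.

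The Intervention section sets out what each arm receives. For the block, "The success criterion of e-SGB is Horner's syndrome", and the patient is watched for at least 30 minutes before induction. For controls, "Patients will not undergo any sham procedures and will only be prospectively visited at a specified time point"; and "The anesthesiologist will cover the corresponding part of the patient with sterile dressings to confuse the follow-up, without any puncture".

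Under Randomization and blinding, the endpoint assessors are blinded, and the "data statisticians, and postoperative treatment team members will be blinded to the treatment group allocation"; the anesthesiologist and neurosurgeons are not. The Trial design section calls the study open-label with blinded endpoint assessment.

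**The concern.** A reader takes the timing sentence as the usual assurance that PP exclusions were made by people who knew neither arm nor result. For the one criterion named, the first half of that assurance cannot hold: a patient recorded as lacking Horner's after e-SGB is an e-SGB patient. The second half is not stated. The blind may be broken long after the 14-day primary outcome has been recorded, so a decision can meet the deadline and still be made with outcomes in view.

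Two things are at stake. First, the PP result may be credited with a protection that it lacks for this criterion, and a listing that reveals the arm could reach statisticians who are meant to be blinded. Second, the named exclusion removes patients from one arm with no counterpart in the other. That can bias the PP comparison even when every decision is honest.

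**Working it through.** **1. Who can meet the named criterion.** The violation is defined by the absence of a sign after e-SGB (Statistical analysis). Controls get a dressing and no puncture (Intervention). The probability that a patient listed for this violation is in the e-SGB arm is therefore 1. The same is true of interrupted or abandoned punctures. Violations possible in either arm may lie under the open-ended end of the list, so this is shown only for the puncture-related criteria.

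**2. What the deadline rules out.** Fixing the list before unblinding rules out choosing exclusions after seeing results by arm. It does not rule out knowledge of individual outcomes, which are evaluated daily and entered on the case report form (Measurements).

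**3. Scale of the trial.** Inputs from the Sample size calculation section: 27% vs 45%, 80% power, two-sided 0.05, 5% loss, total 228.
- n per arm = (0.27×0.73 + 0.45×0.55)×(1.96 + 0.84)²/0.18² = 107.7 (with 0.8416 for 0.84), so 108.
- 108/0.95 = 113.7, so 114 per arm and 228 in total.

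The plan's figure is reproduced, and 108 evaluable per arm is used below.

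**4. One-arm exclusion related to prognosis.** Assumptions, since the article gives no block-failure rate: no true effect, 45% events in both arms, a share f of e-SGB patients without Horner's, and event rate q among them. The rate in the remaining e-SGB patients is (0.45 − f·q)/(1 − f).

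| f | q | e-SGB rate in PP | shift vs 45% |
|---|---|---|---|
| 10% | 65% | (0.45 − 0.065)/0.90 = 42.8% | 2.2 points lower |
| 20% | 65% | (0.45 − 0.130)/0.80 = 40.0% | 5.0 points lower |
| 10% | 55% | (0.45 − 0.055)/0.90 = 43.9% | 1.1 points lower |
| 20% | 55% | (0.45 − 0.110)/0.80 = 42.5% | 2.5 points lower |
| 10% | 25% | (0.45 − 0.025)/0.90 = 47.2% | 2.2 points higher |
| 20% | 25% | (0.45 − 0.050)/0.80 = 50.0% | 5.0 points higher |

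Rejection by the pooled two-proportion z test, q = 65%:
- f = 10%: 97.2 vs 108 patients, standard error 0.0694, shift 0.0222/0.0694 = 0.32. P(Z < −1.64) + P(Z > 2.28) = 0.050 + 0.011 = 6.2% (before rounding the parts).
- f = 20%: 86.4 vs 108 patients, standard error 0.0714, shift 0.05/0.0714 = 0.70. P(Z < −1.26) + P(Z > 2.66) = 0.103 + 0.004 = 10.7%.

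Exact enumeration gives 6.2% and 10.8%. False findings of benefit rise from a nominal 2.5% to 5.1% and 10.4%.

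**5. Two reference cases, by exact enumeration.**
- Exclusion unrelated to outcome, with 2, 5, 11 or 16 e-SGB patients removed: two-sided rejection 0.048, 0.053, 0.050 and 0.051.
- Outer bound, in which every excluded e-SGB patient had the event: 0.052, 0.073, 0.160 and 0.294 for the same numbers. With 11 removed, the expected e-SGB rate is (108×0.45 − 11)/97 = 38.8%.

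Knowing the arm does not in itself raise the error rate. Harm needs a link between exclusion and outcome, through prognosis or through outcome knowledge.

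**The case against.** The strongest reply is that knowing the arm is not knowing the outcome. Horner's is the success criterion and is observable in the 30 minutes before induction. Table 1 schedules block information preoperatively, and the anesthesiologists record baseline and intraoperative data. The criterion is thus a fact that precedes any postoperative outcome. This stands. A reader might infer that exclusions will be outcome-driven; the article does not support that. What remains is narrower: the timing sentence does not tie PP status to the pre-induction observation.

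A reader might also infer that the timing promise is empty. It is not. In an open-label trial with blinded assessors and statisticians, freezing the list before the statisticians are unblinded still prevents choices based on the between-group result.

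That the listing will unblind the statisticians is likewise an inference. The article does not say when the listing is produced or who receives it, and it may be a final reporting table.

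Who decides, the full violation list and the freeze date are often left to the full protocol or analysis plan, which are not shown; their absence is not the point here. The point is a stated protection that the article's own control procedure defeats for the one criterion it names.

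Finally, the figures in step 4 do not measure loss of blinding. The same bias would arise under perfectly blind decisions, and its size and direction depend on assumed inputs. This stands too, and is why it is presented as a separate matter.

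**Conclusion.** The point holds in limited form. For the named violation, PP exclusion cannot be allocation-blind, which conflicts with the statisticians' blinding if they apply the criterion or see the listing early. The sentence also does not exclude outcome knowledge. It does keep its meaning as a freeze before the group comparison is seen.

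Separately, one-arm exclusion can distort the PP result if block failure is related to prognosis: a spurious 2.2 to 5.0 points and about 6% to 11% rejection, assuming no true effect, 45% events, 108 per arm, 10% to 20% without Horner's and 65% risk among them. At 55% risk the shift is 1.1 to 2.5 points. With no link to prognosis, error stays near 5%; with lower risk among those patients, the bias runs against e-SGB. The article gives no failure rate and no reason to expect either direction.

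It matters because every efficacy analysis is reported on the PP set with no stated order of precedence. Nothing here shows that exclusions would be manipulated.

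**What to change.** 1. Keep the timing sentence but reword it. PP status is set only from the Horner's yes/no result recorded at the pre-induction check and from a closed list of violations, by someone without access to outcomes, and is frozen before unblinding.
2. Withhold the listing that reveals the arm from the blinded statisticians until the primary result is final.
3. State that PP is supportive and that the comparison of all randomised patients carries the conclusion.
4. Add a complier-average estimate as a sensitivity analysis, not as a replacement for PP: the risk difference between all randomised patients divided by the share of e-SGB patients with Horner's. Where the randomised difference is zero this estimate is also zero, whatever the prognosis of patients without Horner's. State its assumption that a block without Horner's has no effect, which partial blocks would violate.
5. Retain interrupted and abandoned punctures for items 3 and 4; the Statistical analysis section now removes them from every analysis. Reconcile this with the Intervention section, which excludes failed blocks without naming an analysis set, whereas the Statistical analysis section treats absent Horner's as a PP matter only.

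The cost is one recorded field, a little more analysis and a wider interval than the naive PP one. Patient care is unchanged.

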### Primary outcome

The primary efficacy outcome is the incidence of symptomatic vasospasm within 14 days after aSAH, which is defined as new focal or global neurological dysfunction or a decrease in the Glasgow coma score by more than two points, with angiographic vasospasm on TCD or CTA [34–36]. Symptoms must not be explainable by causes such as primary bleeding, rebleeding, hydrocephalus, fever, infection, electrolyte or metabolic disorders, and surgical complications.

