### Sample size calculation

At our institution, we have observed a symptomatic vasospasm rate of approximately 45%. The cure rate of SGB in the treatment of progressive CVS was reported as 39% in another trial [31]. Therefore, we hypothesize a positive effect size of 40% for e-SGB compared with the baseline rate. Finally, using PASS 15, a total of 228 patients were needed to detect the difference (27% in the treatment arm vs. 45% in the control arm) in the primary outcome with 80% power and a two-sided alpha of 0.05, allowing for a 5% loss to follow-up. An interim analysis will be performed when 50% of the required sample size is recruited.

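### The five-covariate adjustment rule does not fit the CMH primary test, and neither ITT nor per-protocol is named as the primary population

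*Protocol article*

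**What the plan says.** All of the relevant text except the endpoint definition and the design assumptions is in one paragraph, the Statistical analysis section of the protocol article.

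- Endpoint (Primary outcome section): "The primary efficacy outcome is the incidence of symptomatic vasospasm within 14 days after aSAH", which is a yes/no outcome per patient.
- Test: "The primary outcome will be compared between groups using the Cochran–Mantel–Haenszel test". The sentence gives no stratification factor.
- Adjustment: "All analyses will be adjusted by age, sex, preoperative Hunt-Hess score, preoperative Fisher grade, and site of aneurysm". No analysis is exempted.
- Populations: "All efficacy and safety analyses will be analyzed on both a per-protocol and intention-to-treat basis". Neither is called primary, and no rule says that both must be significant.
- Threshold: a p "value less than or equal to 0.05 (two-tailed alpha level) will be considered statistically significant".
- Cox models: "The rates of spasm, death, complications, and length of stay in the hospital and intensive care unit will be compared using Cox proportional hazards models". The type of spasm (symptomatic, TCD or CTA) is not stated.
- Other outcomes: χ² for categorical data, and Student's t or Mann–Whitney for continuous data.

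The Randomization and blinding section stratifies allocation by culprit vessel only, with four sites.

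**The concern.** Two instructions cannot both be followed for the primary outcome. CMH controls for a factor by splitting patients into strata, so a continuous age cannot enter it. The χ², t and Mann–Whitney tests named for other outcomes have no covariate terms at all. The analyst must therefore drop the adjustment, cross many factors into sparse strata, or replace CMH with a regression. The text does not say which.

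The population is also open. With ITT and per-protocol on equal footing at the same threshold, a split result has no prespecified reading. If *spasm* in the Cox sentence includes symptomatic vasospasm, the primary endpoint also has a second model.

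At stake are the precision of the primary test if the rule is applied literally, and control of the 5% error rate if the choice is made after the data are seen.

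**Working it through.** **1. The plan's own sample size.** Inputs from the Sample size calculation section: "27% in the treatment arm vs. 45% in the control arm", "with 80% power and a two-sided alpha of 0.05, allowing for a 5% loss to follow-up". Two-proportion z test, unpooled variance:

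n per arm = (1.960 + 0.842)² × (0.45×0.55 + 0.27×0.73) / 0.18² = 7.849 × 0.4446 / 0.0324 = 107.7, so 108.

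With 5% loss: 108 / 0.95 = 113.7, so 114 per arm and 228 in total, exactly as stated. The pooled-variance formula gives 111 per arm and 234 in total. The size therefore rests on one unadjusted comparison at 0.05, with 2 × 108 = 216 evaluable patients.

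**2. Strata if CMH carried all five factors.** Hunt-Hess has 3 levels (Inclusion criteria) and site has 4 (Randomization and blinding). Sex has 2. Assumed: age cut into 2 groups, Fisher grade with 4 levels.

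2 × 2 × 3 × 4 × 4 = 192 strata; 216 / 192 = 1.1 patients per stratum.

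**3. What that does to the test.** Simulated trials at 27% vs 45%, n = 216. Assumed mixes: site 35/10/35/20%, Hunt-Hess 20/50/30%, Fisher 15/30/30/25%.

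| CMH stratified by | Patients in strata that contribute | Power |
|---|---|---|
| Aneurysm site only | nearly all | about 80% |
| All five factors (192 strata) | about 37% | about 48% (46% to 49% across runs) |

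A stratum contributes only if it contains both arms and both outcomes. About 52% of patients sit in strata with both arms, and about 37% in strata that also have both outcomes.

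**4. False-positive rate if the choice is left open.** Simulation with no treatment effect: 4,000 trials, N = 228, event rate about 47%, and 5% to 20% of the e-SGB arm excluded at random from per-protocol. The exclusion rate, covariate mix and event timing are assumptions. Monte Carlo standard error near 0.05 is √(0.05×0.95/4000) = 0.0034.

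| What counts as a positive result | Rate |
|---|---|
| CMH by site, ITT only | 0.052 |
| CMH by site, ITT or per-protocol | 0.056 to 0.067 |
| CMH, adjusted logistic or adjusted Cox, ITT only | 0.074 |
| Any of those three, ITT or per-protocol | 0.081 to 0.095 |

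If the tests were independent, the bounds would be 1 − 0.95² = 0.0975 for two and 1 − 0.95⁶ = 0.265 for six. The actual figures are much lower because the tests reuse nearly the same data. If significance were required on both populations there would be no inflation, but the text does not say so.

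**5. Length of stay.** As continuous data it falls under t or Mann–Whitney; the next sentence assigns it to Cox. No further arithmetic applies.

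**The case against.** A reader might infer that the trial has no primary test. The document does not support that: CMH is the only test expressly tied to the primary outcome. What is open is the adjustment, the population and the role of Cox.

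A reader might also infer that Cox is definitely a second primary test. The Cox sentence follows the one introducing other outcome data, and its list resembles the secondary outcomes (TCD and CTA vasospasm, mortality, complications, length of stay). It may cover only those. The fair criticism is that *spasm* is undefined and, read literally, includes the primary endpoint.

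Nor does the 48% figure mean that the trial is underpowered. The document nowhere proposes crossing five factors or halving age. The natural stratum is the randomisation factor, and that version delivers the design power.

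The per-protocol exclusions are to be settled before unblinding, which limits selection. A free choice among six analyses is a worst case.

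Finally, one could argue that a Cox model for length of stay mishandles in-hospital death. The article gives no censoring rule, and such a rule is normally left to an analysis plan, so only the double assignment of methods is a finding.

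What survives is text that conflicts with itself. A separate analysis plan may exist, but the published paragraph contains rules that cannot all be carried out, which differs from leaving detail out.

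**Conclusion.** The point holds as a defect of specification. The universal five-covariate rule is incompatible with CMH where age is continuous, and unworkable at about 216 patients if age is categorised and all factors are crossed. It also cannot be applied to χ², t or Mann–Whitney tests. Neither population is ranked.

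The loss from about 80% to about 48% power measures how badly the literal rule would behave under an assumed covariate mix, two age groups and a four-level Fisher grade. The exact figure would move with those assumptions. The cause, nearly as many strata as patients, would remain for any similar number of strata.

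The error-rate consequence is modest: about 0.06 if only the population is open, and about 0.08 to 0.10 if Cox and regression versions also compete as primary. The sample size of 228 is not at fault. The change should be made, because it is cheap and removes any doubt about which p-value decides the trial.

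**What to change.** - State one primary analysis: CMH on the binary 14-day endpoint, stratified by aneurysm site, in all randomised patients, with the Mantel–Haenszel risk difference and its 95% CI.
- Label the per-protocol analysis, a covariate-adjusted logistic regression and any Cox analysis of symptomatic vasospasm as supportive.
- Replace the universal adjustment sentence with a list of the outcomes for which adjustment is intended, each with a regression model that can take the covariates.
- Say which vasospasm outcome the Cox sentence covers.
- Name one method for length of stay.

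Writing the primary population as all randomised patients also means rewording the current ITT definition and the exclusion of failed blocks, which are narrower.

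The cost is wording plus the ethics approval that the Protocol amendment section requires for changes to statistical methods. N stays at 228 and no new data are needed. The change should be dated before any unblinded comparison, including the planned interim analysis if that has not yet taken place.

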### Measurements

The endpoint assessors, who are only responsible for postoperative follow-up, will regularly visit all patients at the planned time points (Table 1). The nurse will check the patients every 4 h. At 10:00 AM every day, the attending neurologist and nurse will evaluate whether the patient experienced symptomatic vasospasm in the last 24 h and record it in the case report form. All patients will receive brain imaging, including CT, CTA, and CTP examination, at least twice, before the operation and 5–8 days after the operation. Postoperative days 5–8 correspond to the peak period of CVS appearance 7–10 days after aSAH. Imaging aims to assess CTA vasospasm, cerebral perfusion, new hemorrhage (if present), and infarction. CT needs to be examined an additional two times, one within 24 h after the operation to assess whether new cerebral infarction or hemorrhage is caused by surgery and one at discharge to assess the occurrence of new cerebral infarction. The assessments will be completed mainly by an independent radiologist. All TCD monitoring will be performed by an experienced and specialized follower on the day before surgery (T0) and on the immediate (T1), 1st (T2), 2nd (T3), 3rd (T4), 5th (T5), 7th (T6), and 9th (T7) days after the operation. Delirium will be documented using the CAM-ICU during the first 3 days after the operation. Additionally, cognitive performance will be assessed at baseline and at 24 h, 7 days, 30 days, and 90 days after surgery using the Mini-Mental State Examination (MMSE). The modified Rankin scale (mRS) will be used to assess patient disability at discharge and at 90 days. The incidence of complications, including myocardial infarction, postoperative rebleeding, moderate and severe brain edema, pulmonary embolism, deep venous thrombosis, SGB-related complications, and unexpected adverse events, will also be recorded. All baseline and intraoperative data will be recorded by the resident anesthesiologists and the attending anesthesiologists who are responsible for recruitment and intervention.

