### Secondary outcomes

The secondary outcomes in the BLOCK-CVS trial include the following:Incidence of TCD vasospasm within 14 days after aSAH [34].Incidence of CTA vasospasm on days 5–8 after the operation [34].Incidence of abnormal perfusion monitored by CTP on days 5–8 after the operationIncidence of new cerebral infarction observed on days 5–8 after the operation and at dischargeContinuous cerebral blood flow velocity monitored by TCD on the day before surgery (T0) and on the immediate (T1), 1st (T2), 2nd (T3), 3rd (T4), 5th (T5), 7th (T6), and 9th (T7) days after the operationThe Mini-Mental State Examination (MMSE) score was assessed at 24 h, 7 days, 30 days, and 90 days after the operationIncidence of delirium as measured by CAM within 3 days after the operationTotal length of stay in the intensive care unit and hospitalModified Rankin Scale (mRS) score at discharge, 30 days, and 90 daysAll-cause mortality up to 90 daysIncidence of complications up to 90 days

See Supplement Part 3 for detailed definitions of all observed indicators.

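### The additional TCD mixed model enters time as a random effect although the contrasts compare planned visits, and the collected MMSE and TCD baselines are not used as covariates, which costs precision in secondary outcomes

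*Protocol article*

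**What the plan says.** All references are to the protocol article.

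- **TCD visits.** Under Secondary outcomes, flow velocity is "monitored by TCD on the day before surgery (T0") and at seven postoperative points, T1 to T7, the last on day 9. Under Randomization and blinding, allocation takes place on the day of surgery, so T0 precedes it.
- **TCD analysis.** Statistical analysis first plans a repeated-measures ANOVA with Tukey-Kramer comparisons for "Postoperative cerebral hemodynamic changes measured at multiple planned time points". It then adds a second model: "repeated-measures ANOVA will be utilized with a mixed-model approach (including time as a random effect"). With it, "the specific comparison of the change in each of those measurements between baseline and any specific time point will be tested using linear contrast".
- **MMSE.** Under Measurements, "cognitive performance will be assessed at baseline and at 24 h, 7 days, 30 days, and 90 days". The secondary outcome is the score at the four postoperative times. Statistical analysis does not name MMSE, so it falls among the other outcomes, for which "continuous data will be analyzed using Student’s *t* test" or by Mann-Whitney U.
- **Covariates.** The same section says that every analysis is adjusted for five variables: age, sex, Hunt-Hess, Fisher grade and aneurysm site. Neither baseline MMSE nor T0 velocity is among them.

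**The concern.** A factor is treated as random when its levels stand for a larger population and the interest lies in their spread. Here the levels are eight named visits, and the individual visit means are the question: the Discussion says TCD is meant to show how the effect of the block develops over time. With visit as a random factor, a value for one visit is a prediction pulled towards the overall mean, and a contrast between two visits is not a contrast of fixed effects. With time as a random linear slope and no categorical visit term, the visits are forced onto a straight line. Neither reading delivers the planned comparison cleanly.

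The sentence on contrasts also names baseline and a time point but not the arms. In a two-arm superiority trial the useful quantity is the difference between arms in that change, or in the baseline-adjusted visit mean.

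The second part concerns efficiency. Two baseline measurements are taken before randomisation and are usually among the best predictors of the later value. Leaving them out as covariates gives wider intervals than the same patients could provide.

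**Working it through.** **1. The plan's own figure.** The only figure to reproduce is the sample size. With 45% against 27%, two-sided alpha 0.05, 80% power and unpooled variance:

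n per arm = (1.960 + 0.842)² × (0.45 × 0.55 + 0.27 × 0.73) / 0.18² = 7.849 × 0.4446 / 0.0324 = 107.7, rounded up to 108.

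108 / 0.95 = 113.7, rounded up to 114 per arm, or 228 in total. This matches, and nothing below changes it. I use 108 evaluable patients per arm from here on.

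**2. Variance of the arm difference.** Let r be the correlation between baseline and follow-up, with equal SD at both times. In units of 2 × SD² / n:

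- post-only comparison: 1
- change from baseline: 2(1 − r)
- baseline as covariate: 1 − r²

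The ratio of covariate-adjusted to post-only is 1 − r². The ratio of covariate-adjusted to change score is (1 − r²) / [2(1 − r)] = (1 + r) / 2. The documents give no r, so the range is an assumption.

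| r | adjusted / post-only | reduction | adjusted / change score | reduction |
|---|---|---|---|---|
| 0.3 | 0.91 | 9% | 0.65 | 35% |
| 0.5 | 0.75 | 25% | 0.75 | 25% |
| 0.7 | 0.51 | 49% | 0.85 | 15% |

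The post-only column is the relevant one for MMSE. The change-score column is relevant for TCD if the contrast is read as change from T0 with no constraint on the baseline means.

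**3. What this means for MMSE.** The difference detectable at 80% power with 108 per arm is 2.802 × √(2/108) = 0.381 SD post-only. Multiplied by √(1 − r²), it becomes 0.364, 0.330 and 0.272 SD at r = 0.3, 0.5 and 0.7.

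**4. Random time, as an illustration.** The inputs are assumed: 108 per arm, eight visits, within-patient correlation 0.5, and arm effects at T0 to T7 of 0, 0, 0, 0, 0.1, 0.38, 0.38 and 0.2 SD. The target is the between-arm difference in change from T0 to T5, truly 0.38 SD.

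- Fixed visits (4,000 simulated trials): mean estimate 0.38 SD.
- Arm-by-visit levels treated as random (same trials): mean prediction 0.28 SD, about 26% too small.
- Straight line in time fitted to the assumed profile: 0.23 SD, about 41% too small.

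These show the direction of the problem. Their size depends on the assumed profile and is not an estimate for this trial.

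**The case against.** Several points on the other side stand.

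- **Loose wording.** The phrase may mean a random patient effect, or a random slope alongside fixed visits, either of which would be acceptable. But the text says neither, and it is the only description of the model.
- **The first-named ANOVA.** It does not call time random. A reader might infer that all TCD tests are wrong; the text supports the criticism only for the additional model.
- **Within-arm contrasts.** A reader might infer that the plan will present within-arm changes as treatment effects. The preceding sentence says that hemodynamic changes will be compared, so a between-arm reading is equally open. The fault is lack of clarity.
- **Baseline as a response.** That T0 enters the model as a response is inferred from the contrast sentence. Even so, this is an accepted approach and unbiased under randomisation. T0 is not discarded, because the contrast uses it.
- **Curve shape.** It is tempting to say that a line cannot fit a rise to days 7 to 10 and a later fall. That peak, in the Discussion, describes when vasospasm occurs, not TCD velocity. Measurements equates postoperative days 5–8 with days 7–10 after onset, an offset of 2, so T7 falls at about day 9 + 2 = 11 and hardly covers a fall.
- **MMSE.** A post-score comparison is valid without baseline.

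The general promise to adjust every analysis does not answer the MMSE point: a t or Mann-Whitney test takes no covariates, and baseline MMSE is not listed. It does mean that part of the gain may already be captured by the listed variables, so the reductions above are upper-end figures.

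**Conclusion.** The concern holds in limited form. The additional TCD model, as written, does not suit the contrasts it is meant to serve, because eight planned visits are entered as random and the between-arm target is not made clear. The handling of the MMSE and TCD baselines is a loss of precision and not a source of bias.

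The loss is 9%, 25% or 49% of the post-only variance, and 35%, 25% or 15% of the change-score variance, at r = 0.3, 0.5 or 0.7. This rests on an assumed r, equal SD at baseline and follow-up, and no prior explanation by the other covariates; with those covariates in the model, the gain may be smaller. If the model constrained baseline means to be equal across arms, the TCD loss would largely disappear, but no such constraint is stated.

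A reader might infer that the trial's main conclusion is at risk. It is not: the primary outcome uses a Cochran-Mantel-Haenszel test, and neither that test nor the total of 228 depends on these choices.

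**What to change.** **TCD:** replace the additional model with a mixed model for T1 to T7. Use fixed effects for arm, categorical visit, arm-by-visit, T0 velocity and the five listed covariates, including aneurysm site. Model within-patient correlation by an unstructured covariance or a patient random effect. Report the between-arm difference with its confidence interval at each visit.

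**MMSE:** analyse the scores at 24 h, 7, 30 and 90 days in the same way, with baseline MMSE as a covariate, in place of the t or Mann-Whitney tests.

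**Cost:** no further patients, visits or measurements, since both baselines are already collected. The Protocol amendment section counts a change of statistical methods among those needing Ethics Committee approval, so a short amendment is required. The article reports the trial as still recruiting, so the change should be made and dated before any unblinded look at these outcomes.
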